### Blinding

Due to the nature of the treatment, the patients cannot be blinded to the allocation group. Similarly, the orthodontists who will treat the patients cannot be blinded, as they will know the type of appliance used. However, the technician who will take and analyse the CBCT image will be blinded to the allocation cone because the images will not include the appliance. The data analyst will be blinded to group allocation.

### Data collection

#### Baseline

We will complete an eligibility Case Report Form (CRF). A Participant Registration Form will also be completed by the clinician. The clinician will also complete the CRF. This will include data on clinical examinations, clinical records, intra- and extra-oral photographs, study models, and CBCT. At the beginning of the treatment with the Herbst appliance, all patients will be photographed with the appliance.

#### In-treatment data

The patients will be photographed after any new mandibular advancement has been done in the appliance during the treatment.

#### End of treatment

At the end of the treatment with the Herbst appliance, the following data will be collected; intra- and extra-oral photographs, study models, and CBCT.

We will also carry out a qualitative analysis of the interventions. This will be done at the end of treatment. Young people will be given the choice to be interviewed on a face-to-face basis at their clinical appointment or via telephone. A semi-structured interview approach is selected due to its flexible and interactive nature. This will be able to encourage the young people to share their experience freely guided by a series of questions. A topic guide will be used in the interviews to ensure that all topics of interests are covered but it will not be followed strictly. The topic guide will evolve as the data collection progresses to suit the emerging themes. Interviews will take a conversational style to empower participants to share their experience without leading questions.

The key steps for the records can be seen in the flow chart for the trial (Fig. 4). This will be used as a reference for the involved in the trial.

**Fig. 4 Fig4:**
[figure not shown]
Key steps flow chart. Showing the pre-treatment, treatment and end-of-treatment records collected. *The mandibular advancement will be done just when necessary

## Outcome measures

### Primary outcome measure

The primary outcome measure will be the change in the position of the lower incisors. This will be assessed by using CBCT that will be performed at the beginning of the treatment with the Herbst appliance (T1) and at the end of the treatment with the Herbst appliance (T2) using the Classic iCAT tomography (Image Sciences, Hatfield, PA, USA).

All the examinations will be obtained with the patient seated with the mandible in a centric relationship. The field of view (FOV) will be a cylinder with a height of 17 cm per 23-cm diameter. The voxels dimensions will be 0.4 × 0.4 × 0.4 mm.

The tomography image archives will be exported in the Digital Imaging and Communication in Medicine (DICOM) format and converted to a GIPL format (Guys Image Processing Lab) using the open source software ITK-SNAP 3.4 (Fig. 5).

**Fig. 5 Fig5:**
[figure not shown]
View from the computer screen with the 3D virtual models done using the software ITK-SNAP 3.4. **a** Axial, sagittal and coronal slices and 3D model in T1. **b** Axial, sagittal and coronal slices and 3D model in T2. **c** Approximated view from T1. **d** Approximated view from T2

Single files will be created in .STL format (StereoLithography) using ITK-SNAP 3.4 software and then in VRML format (Virtual Reality Modeling Language) using a .WRL extension (Virtual Reality World). Next, an automatic superimposition from these models will be made using the software Geomagic Qualify 2013 (Geomagic U.S. Corp, Research Triangle Park, NC, USA). Finally, the superimposition will be obtained through the command Global Registration, which perform the best adaptation of the models (Fig. 6). The entire process of models’ surface registration will be based on the calculation of the smaller distance between the surface’s dots in the time points evaluated, aiming the best adaptation between them automatically (*best-fit*).

**Fig. 6 Fig6:**
[figure not shown]
Superimposition of the mandible. **a** Models in T1 and T2 without registration. **b** Registry of the three points in the mandible. **c** Selection tie tool on symphysis. **d** Regional superimposition using the command Global Registration

For the dental evaluation, the models of the central lower incisors will be imported and superimposed with its respective mandibles using the anterior contour of the chin as a reference (Fig. 7) [17]. After the superimposition, the virtual models will be exported to the .STL format.

**Fig. 7 Fig7:**
[figure not shown]
Dental and mandible superimposition. **a** Incisor surfaces to be superimposed. **b** Molars surfaces to be superimposed. **c** Mandibles from T1 and T2 superimposed showing central incisors and molars

Next, the software STL2Meta, and the software MetaToIV will be utilised to convert these files to META format and next to .IV format (SGI Open Inventor). The files in. IV format will be imported using the software CMF Application (Maurice Müller Institute, Bern, Switzerland) to quantify mandibular and dental changes between the time points. The contour line tool (Isoline) will be used to identify the most displacement occurred in a region of interest (Fig. 8).

**Fig. 8 Fig8:**
[figure not shown]
Isoline tool. **a** Growth in the right condyle. **b** Right condyle in a approximated view showing a growth of 8.04 mm in an upper direction. **c** Lower central incisors showing a displacement of 1.89 mm buccally

### Secondary outcomes measure

To evaluate the bony changes occurring in the mandible, maxilla, the relationship between maxilla and mandible, lower molars and upper molars at the end of the treatment, the same steps used to access the primary outcome measurements will be followed. For the skeletal changes of the mandible, the maxilla and for the relationship between them, the virtual models will be superimposed in the cranial base using the software Geomatic Qualify 2013 (Fig. 9).

**Fig. 9 Fig9:**
[figure not shown]
Print screen of the mandible and the maxilla’s superimposition on the cranial base using the software Geomatic Qualify 2013To evaluate gingival recession in the lower incisor area, comparison between dental casts and photographs from the beginning and the end of the Herbst appliance phase will be done. The presence or absence of gingival recession for each lower incisor will be noted for each lower incisor for each time point. In the presence of recession, a ‘yes’ will be marked. The photographs will be used to confirm [18]To evaluate root resorption, comparison between CBCT from the beginning and the end of the Herbst phase will be used for each lower incisorTo explore young people’s experience of using the two types of Herbst appliance, the following methods will be used:4.1.Self-reported questionnaire about patient discomfort4.2.Semi-structured interviews

#### Administrating self-reported questionnaire about patient discomfort

A 5-point Likert scale will be used to access patient discomfort. Measurements of discomfort will be made at the end of treatment, where a score of 1 indicates ‘no pain’ and a score of 5 ‘severe pain’. A mean score will be calculated for each group and compared to each other using paired Student’s *t* test.

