### Design

The study is a single-center, randomised, assessor-blinded, superiority clinical trial with parallel 1:1 allocation. It involves children with class II malocclusion. We will randomise 40 children aged from 11 to 14 years old to treatment with a Herbst appliance with either dental or indirect skeletal anchorage. All participants will be followed until the end of the functional (Herbst) appliance phase of treatment. The expected flow of patients through the trial can be seen in Fig. 1. The SPIRIT checklist with the recommended items to address in a clinical trial protocol is available (Additional file 1).

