### Randomisation

#### Sequence generation

The randomisation schedule will be prepared and comprise random blocks that are stratified by gender. As a result, the sample will be separated into 10 blocks with four subjects in each.

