### Statistical methods

Patients’ background characteristics as age, gender, as well as their dental and skeletal pre- and post-treatment measures will be summarised using descriptive statistics, such as means, standard deviations, median, and ranges.

Student’s *t* test will be used to compare the changes in lower incisor position between the dental anchorage group and indirect skeletal anchorage group. The results from multivariate analysis, which consider potential confounders, will be reported. The normality of the data will be judged by the Kolmogorov-Smirnov test. Non-parametric equivalent will be applied if any model assumption is not met. The significance level will be set at ≤ 5% and all analysis will be conducted using SPSS statistical software package (version 12.0, Chicago, IL, USA).

Student’s *t* test will be used to assess dental and skeletal differences between the Herbst with dental anchorage and the Herbst with indirect skeletal anchorage. Intra-examiner correlation coefficients (ICC) will be used to evaluate the reliability of repeated measures. A one-sample test will be performed on duplicate measurements to test for systematic errors. The significance level will be set at ≤ 5%.

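### Discomfort scores from two independent parallel arms are assigned a paired t test, although the protocol defines no pairs; an independent-groups test should be named

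*Protocol article*

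**What the plan says.** The Design section describes a "randomised, assessor-blinded, superiority clinical trial with parallel 1:1 allocation" in which children are randomised "to treatment with a Herbst appliance with either dental or indirect skeletal anchorage". Under Sequence generation, allocation is blocked and stratified by gender, and "the sample will be separated into 10 blocks with four subjects in each".

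The discomfort questionnaire subsection (under Secondary outcomes measure) states: "A 5-point Likert scale will be used to access patient discomfort". It gives one time point: "Measurements of discomfort will be made at the end of treatment". It then fixes the analysis: "A mean score will be calculated for each group and compared to each other using paired" Student's t test.

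The Statistical methods section uses a different form for the other comparisons between the same two arms. For the primary outcome, Student's t "test will be used to compare the changes in lower incisor position between the dental anchorage group and indirect skeletal anchorage group". The same unpaired wording covers the dental and skeletal differences. That section also allows a non-parametric equivalent where a model assumption is not met.

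**The concern.** A paired t test analyses one difference per pair, so it needs a rule that says which two scores form a pair. The text compares group with group, so it cannot be read as a before-and-after test within children. Nothing in the protocol links a child in the dental-anchorage arm to a child in the skeletal-anchorage arm. An analyst following the sentence literally would have to line up two columns in some order, and the p value would depend on that order.

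The children's experience of the two appliances is a stated secondary objective. It has two methods, this questionnaire and semi-structured interviews, so this is its only planned quantitative comparison. The skeletal arm also adds mini-implants, so readers will look at comparative discomfort.

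**Working it through.** **1. Is there any pairing?** There are three possible sources, and none supplies one.
- *Within child:* this needs two discomfort scores per child. Only one, at the end of treatment, is planned, and each child has one appliance.
- *By block:* with 1:1 allocation, a full block of four holds two children per arm. No rule says which of the two goes with which.
- *By the fallback:* the non-parametric equivalent of a paired t test is the signed-rank test, which needs the same missing pairs.

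**2. How does the protocol's own sample size treat the arms?** Inputs from Sample size: difference 2 mm, SD 1.65, 5% type I error (two-sided assumed), 90% power, equal allocation.
- Normal approximation: n per arm = 2 × (1.960 + 1.282)² × 1.65² / 2² = 14.3, so 15 per arm, 30 in total.
- Exact independent two-sample t: 15 per arm gives power 0.893 and 16 per arm gives 0.913, so 16 per arm, 32 in total. This is the stated figure.
- Attrition: 32 / (1 − 0.20) = 40, also as stated.
- If 1.65 were instead the SD of paired differences, 10 pairs would already give power 0.925.

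So the stated 32 is an independent-groups calculation. Only the discomfort outcome is treated as paired.

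**3. What does an arbitrary pairing change?** With n per arm, SDs s₁ and s₂, and r the sample correlation created by the list order:
- independent: SE = √[(s₁² + s₂²)/n], df = 2n − 2
- paired: SE = √[(s₁² + s₂² − 2·r·s₁·s₂)/n], df = n − 1

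The numerator, the mean difference, is the same in both. Only r and the degrees of freedom differ, and r comes purely from list order.

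**4. Illustration (assumed scores; the protocol gives no discomfort figures).** There are 20 per arm, with counts for scores 1 to 5 of 2, 5, 6, 5, 2 (mean 3.0) and 4, 7, 5, 3, 1 (mean 2.5). Sums of squares about the means are 26 and 25, so s₁² = 26/19 = 1.368 and s₂² = 25/19 = 1.316.

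| Analysis | SE | t | df | p |
|---|---|---|---|---|
| Independent | √(2.684/20) = 0.366 | 0.5/0.366 = 1.36 | 38 | 0.18 |
| Paired, both arms sorted the same way | √[(5/19)/20] = 0.115 | 4.36 | 19 | 0.0003 |
| Paired, sorted in opposite ways | √[(97/19)/20] = 0.505 | 0.99 | 19 | 0.33 |

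The sum of squared deviations of the differences is 26 + 25 − 2 × 23 = 5 for the same order and 26 + 25 + 2 × 23 = 97 for the opposite order. Over 20,000 random pairings of these scores, the middle 95% of paired p values ran from 0.086 to 0.268 (median 0.188), and 0.45% were at or below 0.05.

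**5. Degrees of freedom and power.** Power is for assumed standardised differences of 0.8 and 1.0.

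| Per arm | df, independent / paired | Critical t, independent / paired | Power, independent | Power, arbitrary pairs |
|---|---|---|---|---|
| 20 | 38 / 19 | 2.024 / 2.093 | 0.69, 0.87 | 0.67, 0.85 |
| 16 | 30 / 15 | 2.042 / 2.131 | 0.59, 0.78 | 0.56, 0.75 |

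**6. Type I error.** With random pairing of assumed 5-point scores under no difference (40,000 simulated trials), the paired test rejected in 5.0% of trials at 16 per arm and 5.2% at 20 per arm. The independent test rejected in 5.0% and 5.1%.

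**The case against.** The best defence is that this is a one-word slip with small consequences. Every other t test between these arms is stated without pairing, the sample size is an independent-groups calculation, and the outcome is one item within a secondary objective. That defence is sound on severity. It does not remove the error, because the protocol names a specific test that does not fit its design.

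Three stronger readings are tempting, and the document does not support them.
- *The error rate is inflated.* A reader might infer this from the range of p values. If the pairing is unrelated to the scores, type I error stays near 5%. The extremes in the illustration come from sorting both columns by score, and random listing gives a much narrower spread. The spread also depends on the data chosen. A data set placed at an independent p of 0.050 would put a large share of pairings on either side of the threshold, but that says nothing about this trial.
- *The test cannot be run once patients drop out.* This would hold for completers only. The Intention-to-treat analysis and imputation section retains all randomised patients and multiply imputes missing data, so the planned set is 20 against 20. Imputation restores the numbers but does not create pairs.
- *A 5-point item rules out a t test.* The independent t test held its level in the simulation above, and Statistical methods already allows a non-parametric alternative. A rank or ordinal method is a reasonable preference, not a correction of an error.

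**Conclusion.** The point stands in a limited form. The protocol names a paired test for two independent arms with a single measurement per child and no defined pairs. As written, the standard error and p value are not determined by the data alone, and degrees of freedom are halved (38 to 19 at 20 per arm, 30 to 15 at 16 per arm). The estimated mean difference is unaffected, and with random pairing the cost is about 2 to 3 percentage points of power. The real weakness is that an analyst's choice of row order could move the result.

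This is a should-fix correction to a secondary outcome. It has no bearing on the primary analysis or on the sample size of 40. The absence of pairing rests on the protocol's text. The sizes rest on assumptions that the protocol does not supply: a two-sided 5% level, the discomfort score distributions, and standardised differences of 0.8 to 1.0.

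**What to change.** In the discomfort questionnaire subsection, replace the paired Student's t test with a two-sample (independent-groups) Student's t test, in line with Statistical methods, and name Mann-Whitney as the non-parametric equivalent. A gender-stratified rank test or an ordinal model with arm and gender is optional, given the 5-point scale and the stratified randomisation.

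The cost is one sentence of wording. No new data, visits or patients are needed, and the sample size does not change. The change should be recorded before the discomfort scores are analysed.

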#### Semi-structured interviews

Semi-structured interviews will be administered to explore young people’s experience of wearing the two types of Herbst appliance. This is to gain insights into users’ views about the treatments and the impacts, if any, that the appliance had on their everyday life.

### Statistical methods

Patients’ background characteristics as age, gender, as well as their dental and skeletal pre- and post-treatment measures will be summarised using descriptive statistics, such as means, standard deviations, median, and ranges.

Student’s *t* test will be used to compare the changes in lower incisor position between the dental anchorage group and indirect skeletal anchorage group. The results from multivariate analysis, which consider potential confounders, will be reported. The normality of the data will be judged by the Kolmogorov-Smirnov test. Non-parametric equivalent will be applied if any model assumption is not met. The significance level will be set at ≤ 5% and all analysis will be conducted using SPSS statistical software package (version 12.0, Chicago, IL, USA).

Student’s *t* test will be used to assess dental and skeletal differences between the Herbst with dental anchorage and the Herbst with indirect skeletal anchorage. Intra-examiner correlation coefficients (ICC) will be used to evaluate the reliability of repeated measures. A one-sample test will be performed on duplicate measurements to test for systematic errors. The significance level will be set at ≤ 5%.

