### Analysis

#### Sample size

The primary outcome measure is the difference between the post- and pre-treatment position of the lower incisor edge calculated in millimeters. A 2-mm difference in primary outcome between groups is considered to be clinically significant. This value was obtained based on the clinical judgment of 18 dental professors, senior and junior lecturers, and post-graduate students via interviewing. The standard deviation of such difference was reported in the academic literature to be 1.65 [15]. Allowing for 5% type 1 error, 90% power and equal size allocation among groups, 32 subjects will be required. Considering a 20% attrition rate the total number of recruitment will be 40, with 20 in each group. This calculation was done using online open source software developed by Harvard University [16].

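### Randomisation is stratified by gender, but the only test named for the primary outcome leaves gender out; this is a conservative loss of precision that a gender term removes at almost no cost

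*Protocol article*

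**What the plan says.** Under Sequence generation, the schedule will "comprise random blocks that are stratified by gender", in ten blocks of four.

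Under Sample size, the primary outcome is "the difference between the post- and pre-treatment position of the lower incisor edge calculated in millimeters". The target difference is 2 mm and the standard deviation 1.65: "Allowing for 5% type 1 error, 90% power and equal size allocation among groups, 32 subjects will be required". Allowing for 20% attrition, 40 are recruited.

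Under Statistical methods, Student's t test "will be used to compare the changes in lower incisor position between the dental anchorage group and indirect skeletal anchorage group". No stratum or covariate is attached to it. The next sentence adds: "The results from multivariate analysis, which consider potential confounders, will be reported". The section does not say which of the two carries the conclusion. Age, gender and pre-treatment measures otherwise appear there only for descriptive summary. The skeletal and dental secondary outcomes are also compared by t test.

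**The concern.** Stratified blocks force the arms to be nearly balanced on gender. Differences between boys and girls therefore add almost nothing to the real sampling variation of the treatment difference. A two-sample t test does not use this: it pools the spread within each arm, and that spread includes the boy-girl difference. If gender is prognostic, the test reports more uncertainty than the design has.

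At stake is precision in a trial of 40 children: a wider confidence interval around the mm difference, and a test that runs below its nominal 5%. A lesser point is that a second, adjusted result for the same endpoint is promised without an explicit statement of which is primary.

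**Working it through.** **Inputs.** From Sample size: difference δ = 2 mm, SD σ = 1.65 (unit not given, mm assumed), alpha 5% (two-sided assumed), power 90%, 32 evaluable, 40 recruited. From Sequence generation: stratification by gender, blocks of four. Assumed, because the article gives no figure: the share of outcome variance explained by gender, R² = 0, 0.1 or 0.2, and equal numbers of boys and girls.

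**1. The plan's own figure.** Normal approximation, per arm: n = 2[σ(z₀.₉₇₅ + z₀.₉₀)/δ]² = 2[1.65 × (1.960 + 1.282)/2]² = 14.3, so 15 per arm (30 in total). The exact noncentral-t calculation gives 89.3% power at 15 per arm and 91.3% at 16, so 16 per arm = 32. Inflation: 32/(1 − 0.20) = 40. The stated sample size reproduces, and it rests on an unadjusted two-group comparison.

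**2. Standard error.** With 16 per arm the t test works with about σ√(2/16) = 1.65 × 0.3536 = 0.583 mm. With gender balanced by design, the real standard error is 0.583 × √(1 − R²):

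- R² = 0.1: 0.553 mm, so the t test overstates it by about 5% (1/√0.9 = 1.054).
- R² = 0.2: 0.522 mm, so the t test overstates it by about 12% (1/√0.8 = 1.118).

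**3. Type I error of the t test.** Rough check on 30 df: the critical value 2.042 acts as 2.042/√(1 − R²). This is 2.153 at R² = 0.1 (two-sided tail 4.0%) and 2.283 at R² = 0.2 (3.0%). Simulation with gender balanced within each arm agrees.

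**4. Power at the planned 2 mm, 16 per arm.** The unadjusted columns at R² = 0.1 and 0.2 are simulated. Power with a gender term is noncentral-t with residual SD 1.65√(1 − R²) on 29 df.

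| Gender R² | Type I, t test | Type I, with gender | Power, t test | Power, with gender |
|---|---|---|---|---|
| 0 | 5.0% | 5.0% | 91.3% | 91.2% |
| 0.1 | 3.9% | 5.0% | 92.2% | 93.7% |
| 0.2 | 2.9% | 5.1% | 93.2% | 95.9% |

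**5. A second covariate.** With two terms (28 df) that explain nothing, power at 32 evaluable is 91.1%, and 16 per arm still suffices for 90%. The required sample size does not rise.

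**6. Analysed number.** The article plans to analyse all randomised children with multiple imputation, so 16 per arm is the low end. At 20 per arm with complete data, the t test's type I error is about the same (3.8% and 2.9%), and power is 96.8% against 97.6% (R² = 0.1) and 97.5% against 98.7% (R² = 0.2).

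**The case against.** The case for leaving the plan alone is substantial.

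- **The t test is not invalid.** Its error is on the cautious side, and at the planned 2 mm it keeps at least 91% power in every scenario above. A reader might infer bias, inflated false positives or an underpowered trial. The documents support none of these, and the stated sample size is right for the test it assumes. This objection stands in full and limits the point to precision.
- **The gain depends on an R² that the article does not give.** This stands. If gender is not prognostic, the t test's standard error is correct. Adding gender then costs only about 0.1 point of power, so the choice does not require knowing R².
- **The ranking can be inferred.** The t test is named first and matches the sample size calculation, and the adjusted result is promised as an additional report. This largely stands. A reader might infer room for selective emphasis, but committing to report both results limits it. An explicit statement would still be better.
- **The covariates may be named elsewhere.** A condensed article commonly leaves the covariate list and model form to the analysis plan, and gender may well be on that list. Their absence is no fault here.
- **A baseline incisor covariate may not be free.** The T1 scan already enters through the change score. The described image processing superimposes T1 and T2 models and reads displacement; it defines no T1 inclination angle. Adjusting for inclination would need a new measurement, so it should not be part of the recommendation.

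What remains is the mismatch between two things the article does fix: the stratified randomisation and the unstratified test.

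**Conclusion.** The point holds as a nearly free improvement, not as an error that threatens the result. The analysis named for the primary outcome does not use the factor by which the trial randomises. If gender explains 10% to 20% of the variance in incisor change, the t test overstates the standard error by about 5% to 12%, runs at a true 3.9% to 2.9% instead of 5%, and gives up about 1.5 to 2.7 points of power at 2 mm. Planned power is met either way. These sizes rest on the assumed R², equal gender numbers and 16 evaluable children per arm. A reader could make the loss look larger by taking a true effect below 2 mm, but 2 mm is the only target the article sets.

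**What to change.** State one primary analysis: a linear model of change in incisal-edge position on arm and gender. One prespecified baseline measure that the trial already records may be added; overjet is an example, since it is assessed for eligibility. Report the adjusted difference in mm with its 95% CI, to be read against the 2 mm target. Keep the unadjusted t test as a supportive analysis and say so. Use the same gender-adjusted model for the skeletal and molar change outcomes.

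The cost is a few lines of wording and one or two degrees of freedom. No new measurement is needed and the sample size does not change. The choice should be fixed before the analyst sees outcome data by arm.

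### A Kolmogorov-Smirnov check on 16 to 20 patients per arm decides whether the primary analysis is a t test or an unnamed non-parametric test, so the primary effect measure is not fixed, although the trial is sized on a 2-mm mean difference

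*Protocol article*

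**What the plan says.** All references are to the protocol article.

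- **Outcome (Sample size).** The outcome is defined on the mm scale: "The primary outcome measure is the difference between the post- and pre-treatment position of the lower incisor edge calculated in millimeters".
- **Target and spread (Sample size).** On the effect to detect, the section says: "A 2-mm difference in primary outcome between groups is considered to be clinically significant". The assumed SD is 1.65, taken from published work.
- **Numbers (Sample size).** The evaluable size is given as follows: "Allowing for 5% type 1 error, 90% power and equal size allocation among groups, 32 subjects will be required". Planned attrition of 20% then raises recruitment to 40, or 20 per arm.
- **Default test (Statistical methods).** Student's t test is the default; in the plan's words, it "will be used to compare the changes in lower incisor position between the dental anchorage group and indirect skeletal anchorage group".
- **The check (Statistical methods).** The only check named is this one: "The normality of the data will be judged by the Kolmogorov-Smirnov test". The text does not give the level, whether the Lilliefors correction for an estimated mean and SD applies, or whether the check is run per arm, on pooled values or on residuals.
- **The switch (Statistical methods).** The consequence of a failed check is: "Non-parametric equivalent will be applied if any model assumption is not met". The replacement test and the estimate to go with it are not named.
- **Missing data (Intention-to-treat analysis and imputation).** All randomised patients are analysed, with missing values filled by multiple imputation.

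**The concern.** This is a stated rule, not a detail left open. A preliminary significance test on the outcome selects the primary analysis. The trial is designed around a mean difference in mm. A rank test, the natural reading of a non-parametric equivalent to the two-sample t test, does not estimate that quantity. After a switch, the protocol names no estimate to compare with the 2-mm threshold.

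A normality test at this sample size is also a poor guide. It can miss moderate departures, and it sometimes rejects data that are normal. The trigger is wider than the named check as well, because it covers any model assumption, and no other check is specified. At stake is whether the headline result answers the question the trial was sized for.

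**Working it through.** **1. The plan's own figure.** Inputs from Sample size: difference 2 mm, SD 1.65, type I error 5% (two-sided assumed, as sidedness is not stated), power 90%, 1:1 allocation.

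- Normal approximation: n per arm = 2(1.960 + 1.282)² × 1.65² / 2² = 14.3, so 15 per arm, 30 in total.
- Exact t: noncentrality = (2/1.65) × √(n/2). At n = 15 it is 3.320 and power is 89.3%. At n = 16 it is 3.428 and power is 91.3%. So 16 per arm, 32 in total.
- Attrition: 32 / (1 − 0.20) = 40.

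The stated 32 and 40 are reproduced by a two-sided t-test calculation. The design quantity is therefore a mean difference in mm.

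**2. How the check behaves.** The protocol gives no outcome distribution, so the shapes are assumptions. Each row uses 20,000 simulated trials with the same shape in both arms, a 5% check in each arm, and a switch to Mann-Whitney if either arm is rejected. Paired entries are for 16 / 20 per arm.

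| Shape | Lilliefors rejects one arm | Uncorrected K-S rejects one arm | Test switched (Lilliefors, either arm) | Type I error, two-stage (Lilliefors) |
|---|---|---|---|---|
| Normal | 5% / 5% | 0% / 0% | 9.5% / 9.4% | 0.050 / 0.052 |
| t, 5 df | 12% / 13% | 0.3% / 0.4% | 22% / 25% | 0.051 / 0.052 |
| Gamma, skewness 1 | 15% / 18% | 0.1% / 0.2% | 28% / 33% | 0.054 / 0.053 |
| Log-normal, σ 0.5 | 27% / 34% | 0.9% / 1.4% | 47% / 57% | 0.055 / 0.051 |
| Exponential | 48% / 58% | 2.0% / 3.6% | 73% / 83% | 0.056 / 0.054 |
| Log-normal, σ 1 | 69% / 79% | 12% / 20% | 90% / 96% | 0.052 / 0.050 |

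The normal row agrees with arithmetic: two independent 5% checks give 1 − 0.95² = 9.75%.

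**3. Different shapes in the two arms, equal means, 20 per arm.** Type I error of the two-stage rule (Lilliefors / uncorrected):

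- exponential against normal: about 0.07 / 0.056
- log-normal (σ 0.5) against normal: 0.064 / 0.053
- a mixture with 25% of patients shifted by 2.5 SD, against normal: 0.059 / 0.052

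**4. Does the t test need the check?** With no check, its type I error was 0.037 to 0.052 across the same-shape cases and reached about 0.056 when the arms differed in shape. Its power for 2 mm at SD 1.65 is 91.3% with 16 per arm and 96.2% with 20.

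**5. Does the choice of test matter at the design effect?** With a true 2-mm shift, the two tests disagreed on significance in 1.8% (normal, 20 per arm) to 8.7% (log-normal σ 1, 16 per arm) of trials. A repeat run put the lower end near 1%. Power, t against rank, at 16 / 20 per arm:

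- normal: 91.0 v 89.0 / 96.2 v 95.2
- log-normal σ 0.5: 90.5 v 95.6 / 95.0 v 98.6
- exponential: 90.2 v 96.6 / 94.7 v 98.9
- log-normal σ 1: 91.1 v 99.6 / 93.5 v 99.9

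**6. Side by side with imputation.** At the planned attrition, 40 − 32 = 8 outcomes could be imputed. Each completed dataset contains different values, so the check can pass in some and fail in others. The protocol does not say which result governs.

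**The case against.** The rule is prespecified: a default test, a named check and a fallback. Only the branch taken depends on the data, and the Blinding section keeps the analyst unaware of allocation, which limits steering. This stands. A reader might infer post hoc test selection or a materially inflated type I error, and the documents and figures support neither. The excess is under one percentage point in the same-shape cases. About 0.07 needs exponential data in one arm only plus the Lilliefors form, and nothing in the protocol points to that shape. Some difference in shape is possible, since Safety reporting foresees mini-implant failure and only one arm has mini-implants, but the mixture that mimics it gives 0.059.

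A reader might also infer that the check misses gross skewness and so leaves the t test unprotected. That fails on both parts. The Lilliefors form finds exponential data in 48% to 58% of single arms, and the t test holds its level without any check. Nor do the two drawbacks occur together: the uncorrected form seldom fires, so the t test is nearly always kept, while the corrected form detects marked skewness but switches often.

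It would also go too far to say that no result in mm could be reported after a switch. Descriptive means and medians are promised, a multivariate analysis is promised too, and a non-parametric shift estimate in mm exists. None of these is designated as the primary estimate.

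Finally, the pooling of rank-test results across imputations may be settled in an analysis plan that is not shown, so its absence is not an error here. What remains is that the stated switch fits awkwardly with the stated imputation.

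**Conclusion.** The point holds as a weakness in how the primary analysis is fixed, not as a threat to validity. The primary test and its effect measure depend on a check of unstated version, level and scale, while the design is for a mean difference. Under the assumed shapes:

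- the Lilliefors form changes the test in 9% to 10% of trials where it should not;
- the uncorrected form rejects 4% or less of single arms, except with log-normal σ 1 (12% / 20%);
- the t and rank verdicts differ in about 1% to 9% of trials at the 2-mm effect;
- type I error is about 0.048 to 0.057 for most shapes, and about 0.07 in the one extreme case.

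These figures assume a per-arm check at 5% and Mann-Whitney as the fallback. A check on pooled values or residuals would behave differently. The change is worth making because it costs only wording and the check gives the t test no protection that it needs.

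**What to change.** In Statistical methods, delete the Kolmogorov-Smirnov gate and the switch. State one primary analysis: the between-group mean difference in change in lower incisor position, in mm, with a 95% CI, from a Welch t test or a linear model, estimated in each imputed dataset and combined across imputations. Name a rank test and report it as a sensitivity analysis only. Inspect residuals graphically, and say that the inspection does not select the test. A permutation or bootstrap p value is optional.

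The cost is protocol or analysis-plan wording, with no extra patients or data. The sample size stays at 32 evaluable and 40 recruited. The downside is lower efficiency with strongly skewed data: about 4 to 6 points of power against ranks in the exponential and log-normal σ 0.5 cases (for example 96.6 − 90.2 = 6.4), and up to 99.6 − 91.1 = 8.5 points with log-normal σ 1. Even there the t test kept at least 90% power for 2 mm, and the rank sensitivity analysis would show the discrepancy.
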